## Abstract

**Background:**

Mobile technologies have become capable of changing the paradigm of healthcare services. A clear example is that, nowadays, these technologies are an important instrument for data collection processes, epidemiologic surveillance, health promotion and disease prevention. Therefore, technological tools should be exploited to optimize the monitoring of patients with chronic diseases, including patients who require home oxygen therapy. Purpose: The purpose of this study is to determine the efficacy of a mobile application in the clinical monitoring of patients under home oxygen therapy.

**Methods:**

This is a randomized controlled trial includes subjects of 18 years or older diagnosed with Chronic Obstructive Pulmonary Disease (COPD) who are under home oxygen therapy. Subjects will be divided into two arms: the intervention group will include patients who will be monitored with a mobile application, and the control group will include patients monitored by conventional follow-up methods (periodic visits of a respiratory therapist). The following outcome variables will be considered to measure the effect of the intervention: identification of dyspnea self-management, number of acute exacerbations associated with oxygen therapy, and the occurrence of oxygen supply underuse.

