### Sample size estimation

A total of 32 subjects (16 for the experimental group and 16 for the control group) should be recruited to obtain a 1:1 ratio, 80% power (beta error = 20%) and 95% safety (alpha error = 5%), and assuming according to the results evidenced by Nguyen et al. [28] that intervention in the experimental group will cause a 3% increase, with ± 6 standard deviation, in the identification of dyspnea self-management. A final sample size of 44 subjects (22 for the experimental group and 22 for the control group) has been determined to minimize the effects of potential losses in statistical power.

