Identification of dyspnea self-management and quality of life through the mobile app. Will be evaluated up to 12 weeks, from date of randomization until the date of first documented progression or date of death from any cause, whichever came first, assessed up to 6 months

- Independent variables: medical diagnosis, comorbidities, age, sex, health system affiliation regime, smoking, alcohol use, obesity, social isolation, number of people who live with the patient, caregivers required for the patient’s healthcare, prescription and compliance with oxygen therapy (hours/days), underuse of the oxygen system, level of instruction for the management of the mobile app.

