#### Statistical analysis

A descriptive analysis of the study variables will be performed, characterizing patients, generating graphs and frequency tables for qualitative variables, and estimating measures of central tendency (mean), dispersion (standard deviation) and position (distribution limits and range) for quantitative variables.

For bivariate analysis, a Student’s t test will be conducted to compare two means, whereas a chi-squared test and Fisher’s exact test will be used for qualitative variables. For analyzing three mean values or more, a repeated measures analysis of variance (ANOVA) will be used. Multiple lineal regression models will be applied to adjust the impact of the use of the app and to remove the effect of confusing factors, estimating standardized beta coefficients, an adjusted determination coefficient, and residual values. An alpha error of < 5% will be accepted and 95% confidence intervals (95% CI) will be estimated for all statistical analysis, and the SPSS Statistics software, 25.0 version (IBM Corp) will be used.

**Formal committee**: no need for a formal committee as the trial is short with minimal known risks.

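### Oxygen underuse is named as an effect outcome only as an occurrence, while underuse and the hours data behind it are listed as independent variables; a comparison of hours used against hours prescribed would be more sensitive

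*Protocol article*

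**What the plan says.** The Methods part of the abstract lists the variables by which the effect of the intervention will be judged. After dyspnea self-management come "number of acute exacerbations associated with oxygen therapy, and the occurrence of oxygen supply underuse". Exacerbations are counted; underuse is recorded as occurring.

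The body treats underuse differently. The list of outcomes under Outcome variables contains no underuse item; the nearest is the duration of the oxygen cylinder. The list of independent variables at the end of that section includes "prescription and compliance with oxygen therapy (hours/days), underuse of the oxygen system".

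The Statistical analysis section assigns tests by type of variable, not by name: "a chi-squared test and Fisher’s exact test will be used for qualitative variables", and a Student's t "test will be conducted to compare two means". Multiple linear regression is planned for adjustment. Underuse is not defined, has no cut-off and is not tied to a named test. It is neither the primary nor the key secondary outcome in the trial registration table.

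**The concern.** Two things need attention.

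- **Role.** The same quantity is an outcome in the abstract and an independent variable in the body. If the app changes oxygen use, then entering underuse or compliance as an adjustment variable would remove part of the effect the trial wants to estimate.
- **Scale.** If underuse is use below prescription, a yes/no occurrence is a cut through a continuous measure that the variable list already contains. A patient who moves from very low use to just under the cut counts as unchanged; one who crosses it by minutes counts as a full success.

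With 22 patients per arm, a yes/no test could easily miss a real improvement in hours of use, and a null result might be read as showing that the app does nothing for underuse.

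**Working it through.** **The plan's own figures.** The article gives no underuse rate, SD, expected effect or power, so there is no underuse figure to reproduce. Its only standardised effect comes from Sample size estimation, for another outcome: the intervention is expected to "cause a 3% increase, with ± 6 standard deviation, in the identification of dyspnea self-management". That is d = 3/6 = 0.5. The section's 16 per arm does not follow from it: 2 × (1.960 + 0.842)² / 0.5² = 62.8, or 63 per arm at two-sided 5% and 80% power. This is a separate matter, but it explains why power is low on any scale below.

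**Inputs**
- From the article: "A final sample size of 44 subjects (22 for the experimental group and 22 for the control group", so n = 22 per arm; alpha 5%.
- Assumed: two-sided testing; hours of use (relative to prescription) normal with equal SD; an effect of d = 0.5 carried over from the other outcome, with 0.8 as a second case; 30%, 50% or 70% of controls underusing.

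**Continuous comparison.** The t-test power comes from the noncentral t with 2 × 22 − 2 = 42 degrees of freedom and noncentrality d × √(22/2).
- d = 0.5: noncentrality 1.658, power 36.7%.
- d = 0.8: noncentrality 2.653, power 73.6%.

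**Yes/no comparison.** With control underuse p0, the same shift gives p1 = Φ(z(p0) − d) in the app arm. Power is the summed probability of all pairs of binomial counts (22 and 22) that reject at 5%, for Pearson's chi-squared without continuity correction and for Fisher's exact test.

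| d | p0 | p1 | t test | chi-squared | Fisher | loss, chi-squared | loss, Fisher |
|---|---|---|---|---|---|---|---|
| 0.5 | 30% | 15% | 36.7% | 21.4% | 13.6% | 15.3 | 23.1 |
| 0.5 | 50% | 31% | 36.7% | 24.5% | 16.0% | 12.2 | 20.8 |
| 0.5 | 70% | 51% | 36.7% | 24.3% | 15.9% | 12.4 | 20.9 |
| 0.8 | 30% | 9% | 73.6% | 42.5% | 30.4% | 31.2 | 43.2 |
| 0.8 | 50% | 21% | 73.6% | 51.2% | 39.4% | 22.5 | 34.2 |
| 0.8 | 70% | 39% | 73.6% | 54.5% | 42.0% | 19.2 | 31.6 |

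Losses are in percentage points, taken before rounding the powers.

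**Wider range.** Over d from 0.3 to 1.5, with cut-points at 20% to 50% of the pooled sample or 30% to 70% of controls, the loss ran from about 3 to 33 points with chi-squared and about 5 to 47 with Fisher. The yes/no form lost power in every scenario, but the amount depends heavily on the assumed effect, cut-point and test.

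**The case against.** The strongest reply is that the article never specifies a yes/no test of underuse. The coding is inferred from one noun in an abstract, and the chi-squared and Fisher rule is general. An exact definition may sit in the full protocol or analysis plan. All of that stands. A reader might infer that the trial will test underuse by chi-squared or Fisher and so lose a fixed 12 to 21 points; the documents support neither the certainty nor the figure.

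Second, a reader might infer that the trial already records actual daily hours. The article mentions only compliance in hours/days, with no instrument, and describes its data sources as self-registration, clinical records and a user survey. It also lists compliance and underuse as separate items, and the Background ties underuse of supplies to cost and cylinder requirements. Underuse could therefore mean idle equipment. If so, it is not a cut of the hours variable, and the power comparison does not apply.

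Third, reduced underuse should not be presented as a plainly stated aim. The abstract's Discussion and the main Discussion speak of identifying underuse; the Background says only that it could be avoided with suitable monitoring.

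Fourth, changing the scale does not cure low power: at 0.5 SD the t test has 36.7%. That is correct and limits what the change can achieve.

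These points narrow the finding but do not remove it. The abstract does fix underuse as an effect outcome in occurrence form, the body does file it and the hours data as independent variables, and no passage cites a rule that requires a cut.

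**Conclusion.** The point holds in a limited form and is worth acting on. The article contradicts itself on whether underuse is an outcome or an independent variable, and the only outcome wording it offers is the less informative one.

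If underuse means use below prescription and compliance is recorded in hours in both arms, then at 22 per arm and 0.5 SD the yes/no form gives up about 12 to 15 points of power with chi-squared and 21 to 23 with Fisher, when 30% to 70% of controls underuse. At 0.8 SD the loss is about 19 to 31 and 32 to 43 points. These figures illustrate direction and rough size; the effect and the control rate are assumptions, not trial data.

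Underuse is not the registered primary outcome, and the sample size does not rest on it. The change would improve a weak comparison without making it adequately powered at 0.5 SD.

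**What to change.** 1. Reconcile the abstract with the variable list: make oxygen use relative to prescription an outcome, and do not use it, or underuse, as an adjustment covariate when estimating the app's effect.
2. Define underuse, and state how hours of use are obtained in both arms.
3. Define the outcome as hours used as a percentage of, or minus, prescribed hours. Compare the arms with the t test or linear regression already listed, and report the mean difference with its 95% CI. Add a rank-based or bootstrap check if values are skewed.
4. Report the occurrence of underuse descriptively by arm.

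The cost is wording in the outcome and analysis sections, and no extra patients. No new data are needed provided hours are in fact captured in both arms; if they are not, collection would have to be arranged. A difference in hours or percent is slightly less simple to report than a proportion.

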**Discussion:**

This study is expected to assess the efficacy of a mobile application in the follow up of patients under home oxygen therapy. It will also determine whether the monitoring of a six-month intervention by a team comprising a physician, a nurse and respiratory therapists can decrease acute exacerbations, determine the most appropriate oxygen dose, and identify the underuse of oxygen systems and supplies.

**Trial registration:**

The study has been registered at ClinicalTrials.gov (NCT04820790; date of registration: March 29, 2021)

## Background

Continuous home oxygen therapy (CHOT) is the continuous, general and/or undefined administration of oxygen in the home of patients with chronic hypoxemia. This therapy is aimed at increasing hypoxemic patients’ life expectancy, raising their tolerance to physical activity and decreasing clinical impairment because of reduced blood oxygen levels [1, 2]. In 2001, an increase in the prevalence of Chronic Obstructive Pulmonary Disease (COPD) was observed in Colombia, along with an increase of home oxygen prescriptions for the first stages of therapy, resulting in 3,176 patients enrolled in a home healthcare program. However, no information about their sociodemographic and epidemiologic characteristics is available, which can be explained by the scarce number of epidemiological studies about this therapy. However, González et al. highlight that current prescriptions should be reviewed, and research should be performed to establish guidelines for recommending home oxygen therapy in patients with COPD [3, 4]. In Colombia, the largest COPD registry was created as a result of the Prepocol study (Prevalence of COPD in 5 Colombian Cities Situated at Low, Medium and High Altitude, published in 2008) [5], in which a prevalence of spirometrically defined COPD of 8.9% was estimated. However, no recent data have been collected in new epidemiological studies. It is worth mentioning that the World Health Organization (WHO) described COPD as the third cause of death [6] worldwide, representing a public health concern and one of the primary morbidity and mortality causes. Regarding the costs of hospitalization and COPD exacerbations in Colombia, each exacerbation costs an average of $98, and this value can reach up to almost $700 during hospitalization [7]. Oxygen therapy is essential for COPD management because it can control symptoms, reduce hospital stays and increase survival [8]. However, adherence to this therapy should be consistently monitored. A study performed by Barruecos et al. [9, 10] reported a high rate of noncompliance of patients on home oxygen therapy. Consequently, Mesquita et al. [11] revealed that the quality of life of COPD patients who fail to adhere to oxygen therapy is lower in the long term than that of patients adhering to such therapy. Exacerbations may be observed in patients with COPD, characterized by dyspnea, increased coughing and discharge changes. Moreover, two or more exacerbations per year are considered as acute exacerbations of the disease and have a negative impact on patients’ health. A significant percentage of COPD patients discharged from hospital after an acute exacerbation are readmitted within the next three months, increasing the emergency services attendance rate. Certain factors associated with readmission include poor in-home care, non-adherence to treatment, and limited information about their condition [8, 11]^.^ Therefore, it is essential to develop in-home follow-up and monitoring strategies because home visits allow for a real-time patient examination in the place where therapy usually takes place and are well-accepted by patients [12, 13]. Although the benefits and the clinical and gasometrical criteria for the use of oxygen supplies are well described in literature, the availability of protocols and registry and follow-up instruments for patients hospitalized at home is significantly lesser [1, 3]. Therefore, new healthcare technologies should be used to monitor these patients at home. E-health incorporates information and communication technologies (ICTs) to healthcare products, services, and processes. In this sense, it is defined as the set of ICTs tools that are used in a healthcare environment for prevention, diagnosis, treatment, and follow-up activities, as well as for health management, improving the efficacy of the latter [4]. This term encompasses different healthcare products and services, such as mobile applications (apps) and telemedicine, which includes diagnosis, treatment, and health education. With this technological resource, it is possible to improve healthcare services, save time and money and simplify access of health professionals to remote areas. Moreover, the term “mHealth” should be mentioned as a part of eHealth. Although no standardized definition has been made for this term, the Global Observatory for eHealth (GOe) defined it as a public health medical practice compatible with mobile and wireless devices, such as smartphones, for monitoring patients and the use of virtual assistants [14]. Because mobile health (mHealth) uses smartphones as a complement to medical healthcare, some of its benefits are the possibility of overcoming certain barriers associated with clinical healthcare and adopting technological and innovative interventions to achieve safer clinical practices through resource optimization and patient and/or caregivers’ active participation [15, 16]. These eHealth platforms are an opportunity to develop research, thus providing additional methods to collect, process and analyze health data. Moreover, certain authors focus on the development of new approaches of citizen participation in science [3, 5]. To summarize, it is remarkable that a health professional, patient and/or caregiver use a smartphone and a specific app to access a data source that can be used by the scientific community for their research, thus improving healthcare processes [17]. For the abovementioned reasons, the use of mobile technologies in healthcare is becoming a reality capable of changing the current healthcare paradigm. App functions include data collection, epidemiologic surveillance, patient follow-up, health promotion, disease prevention, access to health data and emergency management [17]. In any case, it seems evident that technologies can address the necessity of achieving a continuous connection in the control of health-disease processes through ICTs [16]. The most innovative aspects of these technologies include real-time information transmission, the possibility to access management guidelines for clinical decision making, and content customization [6]. In a study conducted by Mirkovic et al. [18], aaimed at assessing the usability of Connect Mobile — an app that granted access to an online system providing support to cancer patients in the management of health problems and involved final users in the application design — highlighted the importance, the requirement, and the potential of integrating mobile phones and tablets into patient healthcare systems, as well as of respecting and considering the design suggestions made by users [18]. In this sense, it would be interesting to approach the clinical monitoring of patients on home oxygen therapy through a mobile app aimed at achieving improvements in the treatment, prescription, information, and safety of patients during in-home healthcare processes. Pereira et al. [19], in collaboration with the School of Health Sciences of Universidad de Averio, Portugal, developed Exercit@rt, an app capable of monitoring COPD patients’ real-time heart rate and oxygen saturation levels through a Bluetooth oximeter. Based on this technology, patients can perform, control, geolocalize and assess different respiratory exercises, as well as common daily physical activities. Moreover, this research project incorporated a validation stage involving ten patients with respiratory disorders: five smartphone’s frequent users (SFU) and five smartphone’s non-frequent users (SNFU). The main results revealed that all participants recognized the usefulness of monitoring their disease using the Exercit@rt mobile app [19]. In a literature review about the effectiveness of eHealth interventions in COPD cases, Hallensleben et al. reported a meta-analysis of 10 studies about the teleassistance of this condition, in which a decrease in the number of visits to the emergency and hospitalization rooms was observed as opposed to the control groups receiving regular care [20, 21]. Rassouli et al. [22] digitalized information about patients attending a pulmonary rehabilitation program through a mobile app, which evidenced changes in patients’ quality of life over a of 20-day exercise period. Moreover, Velardo et al. [23] designed an eHealth platform for COPD patients, which also included a mobile app, such that they could manage and control their condition. Patients used the app to complete a symptoms diary, and their oxygen saturation was measured with a wireless pulse oximeter. The clinical trial evidenced a high compliance of self-control during a prolonged period (12 months). Marscha et al. [24] conducted a controlled, randomized trial with an intervention group and a control group of patients with cardiovascular diseases. They designed the Vascular View software to increase self-management behavior of patients with cardiovascular conditions. The intervention group was granted 12-month access to an online self-management software (Vascular View). Assessments took place at baseline and after 6 and 12 months. The results confirmed positive and significant changes over the 12-month period in the intervention group. Arostegui et al. [25] developed an app (PrEveCOPD) to predict adverse events and complications in the short-term progression of patients with COPD. This app is interesting because it shows how clinical prediction measures can be summarized into simple and user-friendly tools, which can be used to estimate the short-term risk of mortality and admission to ICUs. To summarize, it seems evident that health mobile technologies are providing different strategies for the long-term management of chronic diseases, in addition to being convenient, cheap and interactive [26]. Moreover, Bitsaki et al. suggest that technological health tools aimed at chronic patients are a new, sustainable, and innovative business model resulting in significant cost reductions for the health system [27]. Furthermore, the advantages of using technological tools, such as health mobile apps, are that they increase connectivity, reduce the amount of time spent in decision-making, and optimize the use of resources aimed at home healthcare [28, 29]. However, despite the aforementioned positive experiences in the use of mobile apps for different groups of chronic patients, the number of Latin American and Colombian apps is lesser, and this issue should be addressed since most home oxygen supplies are usually underused by patients, which results in an increase of Health System costs and a decrease in coverage based on the requirement for oxygen cylinders. This could be avoided if technological tools with adequate monitoring were incorporated. Thus, we propose this protocol whose purpose is to assess the efficacy of a mobile app in the monitoring of patients under home oxygen therapy through an intervention aimed at decreasing acute exacerbations and increasing self-management of oxygen supplies at patients’ home.

## Methods/design

### Study design

A randomized, controlled, single-blind, two-arm parallel clinical trial will be conducted during six months to assess the efficacy of a mobile application in the follow-up of patients on home oxygen therapy. The control group will include patients on oxygen therapy subject to conventional follow-up methods (regular visits of a respiratory therapist), while the intervention group will include patients followed through conventional methods and through the use of the mobile app “AppO_2_” (Fig. 1).

**Fig. 1 Fig1:**
[figure not shown]
Modified CONSORT flow diagram for individual randomized controlled trials of nonpharmacologic treatments

